### 8.2 Safety monitoring

Trial participants will consent to the use of data captured by the UK Renal Registry (UKRR), NHS Digital (NHSD), Information Services Division Scotland (ISD), Patient Episode Database for Wales (PEDW) and Health and Social Care Services Northern Ireland (HSNI) data. The CTU will collect all events associated with hospital admissions from NHSD, ISD, PEDW or HSNI data as appropriate, and deaths from civil registration (NHSD) on a continuous basis. All hospitalisation-requiring and hospitalisation-associated events, and all deaths, will therefore be captured continuously directly by the CTU.

Given (a) the intensive monitoring of dialysis patients in routine clinical care, (b) the comprehensive data on clinical events recorded directly by the CTU, and c) the routine use of both high-volume HDF

and high-flux HD as part of routine NHS care, the H4RT trial will utilise the following risk-adapted safety reporting approach:

1. Adverse events will be regularly screened for:
  - (a) monthly during recruitment and quarterly during follow-up by the local research team and
  - (b) as directed by the DMC using data collected specifically for the trial and data derived from linkage to routine healthcare databases. .
2. Adverse events (AEs) and serious adverse events (SAEs), i.e. adverse events not considered to be directly related to high-volume HDF, do not require to be recorded and reported (using the standard reporting form) to the sponsor by the PI.
3. Adverse reactions (ARs), i.e. adverse events considered to be directly related to high-volume HDF but not serious, also do not require to be recorded and reported (using the standard reporting form) to the sponsor by the PI.
4. Serious adverse reactions (SARs) and suspected unexpected serious adverse reactions (SUSARs), i.e. adverse events considered to be serious and directly related (or possibly/ probably directly related) to high-volume HDF, however, do require reporting (using the standard reporting form) to the CI and the sponsor as described under 8.3 and 8.4 below. The local research team should maintain a log of SAEs that they identify and agree are not SARs. This will not need to be routinely submitted to the CI but will act as a local record of decision making and may be asked for if a site is monitored.
5. Line listings of SAEs and reported SARs & SUSARs will be reviewed monthly by the CI and submitted annually to the DMC and REC.

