### **8.3 Recording and reporting of unexpected SARs and SUSARs**

All unexpected SARs and all SUSARs occurring from the time of consent until 30 days after the end of the trial must be reported by the PI to the CI and Sponsor within 24 hours of awareness using the SAR/ SUSAR form (see Key Trial Contacts section for emails contact details t). A further review of expectedness will then be undertaken by the CI. The CI will report any reportable SAR and all SUSARs that are related to the research procedures to the Research Ethics Committee and the Sponsor within 24 hours becoming aware of the event. For each reportable SAR and SUSAR the following information will be collected:

- Full details in medical terms and case description;
- Event duration (start and end dates, if applicable);
- Action taken;

- Outcome;
- Seriousness criteria;
- Causality (i.e. relatedness to trial/intervention), in the opinion of the investigator;
- Whether the event would be considered expected or unexpected.

Each reportable SAR and SUSAR must be reported separately and not combined on one SAR/ SUSAR form. Any change of condition or other follow-up information relating to a previously reported SAR/ SUSAR should be documented on the appropriate form (see Key Trial Contacts for email contact details) emailed securely to the CTU and Sponsor as soon as it is available or within at least 15 days of the information becoming available to the research team. Events will be followed up until the event has resolved or a final outcome has been reached.

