### **8.4.1 Principal Investigator/research staff**

Principal investigators (PIs) and research staff at each site will be checking for AEs and ARs when participants attend for treatment /follow-up; they will be responsible for:

- Using medical judgement in assigning seriousness, causality and expectedness. These decisions must involve a medically trained member of the research team and should be recorded on the local log (see 8.2, above).
- Ensuring that all unexpected SAEs, unexpected SARs and SUSARs are documented and reported to the Sponsor within 24 hours of becoming aware of the event and provide further follow-up information as soon as available. Ensuring that unexpected SAEs, unexpected SARs and SUSARs are chased with the Sponsor if a record of receipt is not received within 2 working days of initial reporting.
- Ensuring that all follow up data for reported SAEs, SARs and SUSARs are provided to the CI and sponsor as soon as the event ends or when any new information becomes available.

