## 12 ETHICAL AND REGULATORY CONSIDERATIONS

### 12.1 Research Ethics Committee (REC) review and reports

Ethical and Health Research Authority (HRA) approval will be sought through the HRA for the trial and the qualitative work embedded within the trial. We believe the proposed research does not pose any specific risks to individual participants nor does it raise any untoward ethical issues. As with all trials, the main benefit of participating is an altruistic one to improve care for subsequent patients with kidney failure. As a registry trial, surveillance will be according to routine care. There are no known additional risks for patients in participating, with HDF already a routine part of care in ~15% of cases in the UK and being scaled up. A letter of invitation to participate in the study and a patient information sheet will be developed in collaboration with the PAG and in line with guidance from the HRA. The patient information sheet will provide clear details of the anticipated risks and benefits of taking part in the trial and the study interventions, and may be modified by the findings from the QRI work. The risk and benefits of the study will also be discussed with the local research staff and nephrologists as part of the process of providing written informed consent.

All staff doing specific research activities will be required to complete training in Good Clinical Practice. Informed consent to participate in the trial will be sought and obtained according to Good Clinical Practice guidelines. Informed signed consent forms will be obtained from all participants in all centres, by an appropriately trained individual. Participants will be given sufficient time to accept or decline involvement and will be free to leave the study at any time. Participants who cannot give informed consent (e.g. due to their mental state) will be not be eligible. The participants will be asked to consent to: participation; randomisation; follow up; contact in the future about this and other research; electronic tracing using NHS data; and data linkage with routine NHS data sources.

All research will be performed in accordance with the recommendations guiding biomedical research involving human subjects adopted in the 18th World Medical Assembly, Helsinki, Finland.

Health Research Authority approval will be sought, where appropriate, for any analyses relating to UK Renal Registry data collected under section 251 of the NHS Act 2006 on nonparticipating patients.

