**14.2 Appendix 2 – Risk**

Risks associated with trial interventions

- ☐ LOW  $\equiv$  Comparable to the risk of standard medical care
- ☒ MODERATE  $\equiv$  Somewhat higher than the risk of standard medical care
- ☐ HIGH  $\equiv$  Markedly higher than the risk of standard medical care

Justification:

As high-volume HDF involves infusing an additional 20-25L of water back into the patient x3 per week, x52 weeks per year, water quality is crucial to patient safety and has to meet “Sterile dialysate” standards (i.e. bacterial limits  $<10^6$  CFU/mL & endotoxin limits  $<0.03$  EU/mL). Technological developments over the past decade now make it possible to produce such water “on-line”, i.e. continuously in the renal unit, and almost all renal units in the UK are providing on-line HDF as standard care to at least some patients. There remains, however, a small risk of blood stream infection being introduced as part of the HDF process. This risk is mitigated by renal units monitoring water quality on a regular basis. Any blood stream infections that are believed to be related to the HDF will be reported as SARs.

What are the key risks related to therapeutic interventions you plan to monitor in this trial?

How will these risks be minimised?

| Intervention    | Body system/Hazard     | Activity                                | Frequency | Comments                                   |
|-----------------|------------------------|-----------------------------------------|-----------|--------------------------------------------|
| High-volume HDF | Blood stream infection | Water quality monitoring in renal units | Monthly   | As per UK Renal Association Guidelines (6) |
|                 |                        |                                         |           |                                            |
|                 |                        |                                         |           |                                            |

These risks will also be considered by the DMC and incorporated into data updates they request.

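### Sections 8.3 and 8.4.1 limit the investigator's reporting duty to unexpected serious reactions, while 8.2 item 4 and Appendix 2 set no such limit, so an HDF-related bloodstream infection classed as expected could miss the SAR route

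*Protocol*

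**What the plan says.** Four places in the protocol set the reporting rule for serious reactions to HDF.

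- **Section 8.2, item 4** covers "Serious adverse reactions (SARs) and suspected unexpected serious adverse reactions (SUSARs), i.e. adverse events considered to be serious and directly related" (definitely, probably or possibly) to high-volume HDF. These "do require reporting (using the standard reporting form) to the CI and the sponsor as described under 8.3 and 8.4 below". Expectedness is not a condition.
- **Section 8.3** sets the procedure: "All unexpected SARs and all SUSARs occurring from the time of consent until 30 days after the end of the trial must be reported". Such reports go from the principal investigator (PI) to the CI and sponsor within 24 hours of awareness. The section heading carries the same restriction. The CI then makes a further review of expectedness.
- **Section 8.4.1** gives the site's duty as "Ensuring that all unexpected SAEs, unexpected SARs and SUSARs are documented and reported to the Sponsor within 24 hours" of awareness.
- **Appendix 2** says of HDF that "There remains, however, a small risk of blood stream infection being introduced as part of the HDF process". It makes bloodstream infection the only entry in its monitoring table and adds that "Any blood stream infections that are believed to be related to the HDF will be reported as SARs".

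Two other items in 8.2 bear on the point. Item 2 says that SAEs not considered directly related to HDF need not be reported to the sponsor by the PI. Item 5 provides line listings of SAEs and of reported SARs and SUSARs, reviewed monthly by the CI and sent annually to the DMC and REC.

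**The concern.** The sections disagree on whether an expected serious reaction to HDF has to be reported. The gap matters most for bloodstream infection. Appendix 2 describes it as a remaining risk of HDF, so a PI could reasonably regard it as expected. The same appendix promises that related cases will be reported as SARs.

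At stake is the individual report in which an investigator attributes the event to HDF, made within 24 hours to the CI and sponsor. If some sites follow 8.2 and Appendix 2 and others follow 8.3 and 8.4.1, the count of reported SARs will also vary between sites for reasons unrelated to safety.

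**Working it through.** No sample size, error rate or event count enters this point, so the check is a comparison of the text. Take a serious bloodstream infection that the PI judges related to HDF, and follow it through each section.

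| Protocol section | PI classes it as unexpected | PI classes it as expected |
|---|---|---|
| 8.2 item 4 | Report to CI and sponsor | Report to CI and sponsor |
| Appendix 2 | Report as a SAR | Report as a SAR |
| 8.3 | Report to CI and sponsor within 24 hours | No duty stated |
| 8.4.1 | Report to sponsor within 24 hours | No reporting duty stated; decision recorded on the local log |
| 8.2 item 5 listings | Appears as a reported SAR | Appears as a reported SAR only if someone reported it; may appear as an SAE |

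The first column is consistent. The second is not.

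1. **Which rule would a site apply?** Section 8.2 states the duty and then refers to 8.3 and 8.4 for how to carry it out. A PI who follows that reference reaches the narrower rule.
2. **Is 8.2 just loose wording for the same rule?** Probably not. A SUSAR is already an unexpected serious reaction. Listing SARs separately from SUSARs adds something only if expected SARs are included, and that is the class 8.3 leaves out.
3. **Does the CI's review catch a misclassification?** No. In 8.3 it follows the PI's report, so it cannot reach an event that was never reported.
4. **Does the local log fill the gap?** Only in part. Section 8.2 item 4 describes it as a log of SAEs agreed not to be SARs, which leaves out an expected SAR. Section 8.4.1 sends decisions on seriousness, causality and expectedness to the log, so a site record may exist. The log is not routinely submitted to the CI.
5. **Are the key terms fixed?** Section 8.3 uses the term *reportable SAR* without defining it. The protocol contains no list of expected events and gives no basis for judging expectedness.
6. **What other routes exist?** Under 8.2 the trials unit captures all hospital admissions and deaths by linkage, and adverse events are screened as the DMC directs. Table 2 includes septicaemia admissions and mandated reports for MRSA, MSSA, *C. difficile* and *E. coli*. Appendix 2 says the DMC will consider this risk in the data it requests. Linked data do not carry an investigator's judgement that HDF caused the event, the mandated reports cover only the named organisms, and section 9.6 treats linkage permissions as still being obtained.

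The same sections conflict a second time. Section 8.2 item 2 says SAEs need not be reported to the sponsor. Section 8.4.1 requires unexpected SAEs to be reported to the sponsor within 24 hours, and 8.4.2 has the CI expedite unexpected SAEs to the REC.

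**The case against.** The strongest case on the other side has four parts.

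**The event is not lost.** A reader might infer that a bloodstream infection classed as expected would never reach the CI, sponsor or DMC. The documents do not support that. The listings in 8.2 item 5 include SAEs as well as reported SARs, and a serious infection meets the SAE definition whatever its expectedness. Linkage, mandated reports and DMC-requested data are further routes. This stands, and it limits the loss to the attributed, prompt report.

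**The specific rule should prevail.** Appendix 2 deals with this exact hazard and sets no expectedness condition, so it could be read as overriding the general wording of 8.3. Section 8.3 also asks the form to record whether the event is expected, which suggests that expected SARs may be reported. Both points are fair. But neither 8.3 nor 8.4.1 refers to Appendix 2, and a commitment in an appendix is easily missed by a site working from the procedure.

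**The restriction may be deliberate.** The amendment log entry for version 4.0 describes expedited reporting of unexpected events, with the rest logged locally and captured by linkage. If that is the intention, 8.2 item 4 and Appendix 2 are the passages out of step, and they still need correcting.

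**Expectedness is not settled in the protocol.** No section classes bloodstream infection as expected, and the sponsor's Safety Reporting SOP, which section 8.4 makes applicable, is not available here and may settle the matter. That is so; classification as expected is a possibility, not a stated rule. A reader might also infer from section 12.1 ("There are no known additional risks for patients in participating") that the infection must be unexpected. That sentence concerns the risk of taking part when HDF is already routine care for some patients. It is not an expectedness list and does not support the inference.

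**Conclusion.** The contradiction is real. Section 8.2 item 4 and Appendix 2 require reporting without regard to expectedness; 8.3 and 8.4.1 impose the duty only for unexpected serious reactions. Followed as written, the procedure can defeat the commitment made in Appendix 2.

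The consequence is limited. A related bloodstream infection could miss the SAR route, losing the investigator's attribution to HDF and the 24-hour report to the CI and sponsor, and practice could differ between sites. The event itself can still be seen by other routes. The primary outcome is not affected, because it comes from linked data (sections 3.4 and 7.6).

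No numerical size can be given: the protocol states neither a rate of HDF-related bloodstream infection nor how often sites would call one expected. Bloodstream infection is the only hazard in the Appendix 2 monitoring table, but it is not the only concern the protocol raises about HDF. The Background also mentions loss of solutes and albumin.

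The conclusion assumes that a site follows the reference from 8.2 to 8.3 and 8.4, and that the sponsor's SOP does not already resolve the conflict.

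**What to change.** 1. Reconcile 8.2, 8.3, 8.4.1, 8.4.2 and Appendix 2 so that they state one rule on which SARs the PI reports to the CI and sponsor.
2. Define *reportable SAR*, and state the basis for judging expectedness, either in the protocol or by reference to a named document.
3. Add to 8.3 and 8.4.1 that a bloodstream infection judged related to HDF is reported to the CI and sponsor whatever its expectedness, as Appendix 2 already commits. Use expectedness to decide onward expedited reporting.
4. If expedited reporting of other SARs is meant to be limited to unexpected ones, say so in 8.2 item 4 and state where expected SARs are recorded and how they enter the listings.
5. Reconcile 8.2 item 2 with 8.4.1 and 8.4.2 on whether unexpected SAEs are reported to the sponsor.

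The cost is a wording amendment, a note to sites and a few more SAR forms. The design, the sample size and the primary analysis do not change.

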## **8.4 Responsibilities**

Adverse events will be documented and reported in accordance with North Bristol NHS Trust's Safety Reporting SOP.

### **8.4.1 Principal Investigator/research staff**

Principal investigators (PIs) and research staff at each site will be checking for AEs and ARs when participants attend for treatment /follow-up; they will be responsible for:

- Using medical judgement in assigning seriousness, causality and expectedness. These decisions must involve a medically trained member of the research team and should be recorded on the local log (see 8.2, above).
- Ensuring that all unexpected SAEs, unexpected SARs and SUSARs are documented and reported to the Sponsor within 24 hours of becoming aware of the event and provide further follow-up information as soon as available. Ensuring that unexpected SAEs, unexpected SARs and SUSARs are chased with the Sponsor if a record of receipt is not received within 2 working days of initial reporting.
- Ensuring that all follow up data for reported SAEs, SARs and SUSARs are provided to the CI and sponsor as soon as the event ends or when any new information becomes available.

### **8.4.2 Chief Investigator**

The chief investigator will be responsible for:

- Review the reported SAEs, SARs and SUSARs monthly, considering the overall safety of participants in the trial and updating the Sponsor, oversight committees and sites as appropriate.
- Using medical judgement in assigning seriousness, causality and expectedness of SAEs, SARs and SUSARs where it has not been possible to obtain local medical assessment.
- Using medical judgement in assigning expectedness.
- Immediate review of all reportable SAEs, SARs and SUSARs.
- Ensuring safety reports are prepared in collaboration with appropriate members of the TMG group for the main REC and DMC.
- Reporting safety information to the independent oversight committees identified for the trial (DMC and TSC).
- Expedited reporting of unexpected SAEs, unexpected SARs and SUSARs to the REC within required timelines.
- Notifying PIs of unexpected SAEs, unexpected SARs and SUSARs that occur within the trial.
- Central data collection of SAEs, SARs and SUSARs.

#### **8.4.3 Sponsor**

The sponsor will be responsible for overall oversight of the trial.

#### **8.4.4 Trial Steering Committee (TSC)**

In accordance with the Trial Terms of Reference for the TSC, this group will be responsible for periodically reviewing safety data and liaising with the DMC regarding safety issues.

#### **8.4.5 Data Monitoring Committee (DMC)**

In accordance with the Trial Terms of Reference for the DMC, this group will be responsible for periodically reviewing overall safety data to determine patterns and trends of events, or identifying safety issues, which would not be apparent on an individual case basis.

## **9 STATISTICS AND DATA ANALYSIS**

### **9.1 Sample size calculation**

We anticipate that at 3 years of follow-up 65% of patients on HD will have experienced our composite endpoint and we plan to detect a HR of 0.75. This effect size was agreed to be clinically significant at an investigator meeting involving patients and health care professionals. We assume any effect will be attenuated by (i) cross-over between arms (15% HD to HDF & 5% HDF to HD) and (ii) participants being allowed to take part in other trials simultaneously. To optimise recruitment and avoid excluding eligible patients because they are already participating /want to participate in other trials, an additional adjustment has been made that assumes up to half of patients in both groups will take part in another trial that assigns half of these to an intervention that reduces our composite end-point (HR=0.9), the anticipated proportion experiencing an event on HD will be 62.5% (37.5% surviving event-free) & on HDF it will be 54.1% (45.9% surviving event-free) giving a revised HR of 0.79. The number of events required to detect this difference with 90% power and a 5% significance level is 801, which requires 1348 participants in total. The primary analysis will be intention to treat and to avoid informative censoring participants will not be censored for transplant (10). Allowing for 10% loss to follow-up for other reasons we require 1527 participants and will recruit 1550.

## 9.2 Planned recruitment rate

### The High-volume Haemodiafiltration vs High-flux Haemodialysis Registry Trial

[figure not shown]

**Figure 3 Screening and eligibility numbers**

Recruitment will begin in all sites in month 7 and continue for at least 18 months, as required to recruit the required sample size. The number of potentially eligible patients has been estimated on the following basis:

- Potential participants in the 20 or more participating sites.** On 31st December 2014, there were 24,166 patients on in-centre haemodialysis in the UK (44). In that year, 7,411 patients started in-centre HD (44), with a similar number starting each year. This means that each renal

unit (n=71) will have an average of 497 patients available for screening during the 18-month recruitment period, i.e.  $((24,166 + (7,411 \times 1.5)) / 71)$ . With 20 or more sites recruiting, we would therefore expect 9,939 potential participants across all sites over at least 18 months, as required to recruit the required sample size (i.e.  $497 \times 20$ ), slightly more than the 9,118 required (Figure 3).

- **Eligibility criteria**

- *Potential to achieve high-volume HDF.* Good vascular access in the form of an arteriovenous (AV) fistula or graft is essential for achieving high convection volumes; vascular access in the form of a dialysis catheter makes it very difficult to achieve these volumes. On 31st December 2013, 76% of HD patients in the UK were dialysing on either an AV fistula or graft (45). Considering such patients, it has been shown that 87% of those with an AV fistula can achieve substitution volumes of  $21+L$  (i.e. convection volumes of  $23+L$ ) and 83% of those with an AV graft (14). These patients are likely to be easily identifiable in advance as the blood flow in their access – something integral to the routine dialysis prescription – will be known to be lower than required. We can therefore assume that 65% of patients on HD in a dialysis unit will be considered able to meet the target convection volume, i.e. 86% of 76%.
- *Other exclusion criteria.* It is estimated that a further 20% will be ineligible for other clinical reasons such as clinician predicted prognosis of less than 3 months, a living kidney donor transplant scheduled within 3 months, or transition to home haemodialysis or peritoneal dialysis planned.

Combining these two broad categories of criteria excludes 55% ( $35\% + 20\%$ ) of potentially eligible patients, leaving 4,104 patients (i.e.  $9,118 \times 0.45$ ).

- **Patient agreement to participate.** Recognising the potential barriers to recruitment in this trial the QRI has been incorporated (see Section 7.7). We have anticipated an initial participation rate of 30% in months 1-4, increasing to 40% in months 5 - end of recruitment with the incorporation of lessons learned from the QRI. We anticipate a recruitment period of at least 18 months (or as long as is required to achieve the required sample size).

A screening log compiled by the BTC and QRI researcher, will document the patients assessed for eligibility for the trial, including those approached, those given the study information, and those visited by the nurse. These eligibility details, along with rates of recruitment (percentage of eligible patients agreeing to randomisation) and reasons for patients not consenting to participate will be described in reports sent monthly to the TMG. They will also be used in reviews of participating sites as required.

